### **Design**

An exploratory pilot study of six patients with moderate to severe ME/CFS. After inclusion, there will be an initial 12-weeks observational run-in period, followed by administration of 4 subcutaneous injections of the anti-CD38 antibody daratumumab with 2-week intervals. Patients will be subject to clinical follow-up for 40 weeks from start of intervention. Four additional patients will receive the same intervention, and if they show improvement of ME/CFS symptoms by clinical evaluation six weeks after the fourth injection (at study week 24), they will receive three additional maintenance daratumumab injections at weeks 26, 34 and 42.

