### **End of study**

The study ends when the last included patient has completed their final visit after 52 weeks. For patients with clinical improvement at week 24, who receive additional three daratumumab injections at weeks 26, 34 and 42, the follow-up period will be extended to week 72.

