### Women of childbearing potential

For women of childbearing potential, a serum pregnancy test at baseline must be negative. A woman is considered of childbearing potential (WOCBP), i.e. fertile, following menarche and until becoming post-menopausal unless permanently sterile. Permanent sterilization methods include hysterectomy, bilateral salpingectomy and bilateral oophorectomy.

A postmenopausal state is defined as no menses for 12 months without an alternative medical cause. Highly effective contraceptive measures include: combined (estrogen and progestogen containing) hormonal contraception associated with inhibition of ovulation; progestogen-only hormonal contraception associated with inhibition of ovulation, intrauterine device (IUD), intrauterine hormone-releasing system (IUS), bilateral tubal occlusion, vasectomized partner, sexual abstinence.

Women of childbearing potential must use effective contraceptive methods for at least 4 weeks before start of treatment and at least 24 weeks following the administration of the last daratumumab injection. A man who is sexually active with a woman of childbearing potential must use a barrier method of birth control for at least 4 weeks before start of treatment and for 24 weeks after intervention.

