### Daratumumab intervention

After 12 weeks’ run-in, patients will start intervention.

The first two patients will receive two subcutaneous injections of daratumumab two weeks apart, followed by an observation period of four to six weeks. If there is no serious, unexpected toxicity, we will proceed with another two injections two weeks apart.

After these two patients have received the planned four daratumumab subcutaneous injections, the Safety board will review the data.

Subject to a favorable Safety board review, the pilot study will proceed with the four remaining patients, who will receive four subcutaneous injections of daratumumab two weeks apart.

Thus, all patients will receive in total four subcutaneous injections of daratumumab.

According to a second amendment to the protocol, among four additional patients included, provided clinical improvement at week 24, these will receive additional three daratumumab injections, at weeks 26, 34 and 42, and with extended follow-up until week 72.

The injections will be administered in the outpatient clinic in the Department of Oncology and Medical Physics at Haukeland University Hospital.

Oral premedication will be given at least one hour before daratumumab injection. Before the first daratumumab injection: Dexamethasone 10 mg orally, Cetirizine 10 mg orally, Paracetamol 1 g orally, Montelukast 10 mg orally. Also, at least 20 minutes before daratumumab: Dexchlorpheniramine 5 mg iv.

On the following two days (2 and 3): Dexamethasone 4 mg orally.

Before the second and subsequent daratumumab injections, if no reaction to the first injection: Dexamethasone 10 mg orally, Cetirizine 10 mg orally, Paracetamol 1 g orally.

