#### Assessment during follow-up

After inclusion, patients will complete the questionnaires (SF36, DSQ-SF, self-reported Function level) at 2-week intervals for the first 28 weeks, then at 4-week intervals for the remaining 24 weeks (until 52 weeks). For the additional four included patients (according to amendment 2), if clinically assessed improvement at week 24, there will receive additional three daratumumab injections as described, and with prolonged follow-up until week 72.

Steps per 24h, Resting heart rate, and Heart rate variability will be registered by mean (and SD) per 2-week intervals for the first 28 weeks, then at 4-weeks intervals for the remaining 24 weeks (or 44 weeks if given maintenance) of the study.

Patients will be assessed at the outpatient clinic, Dept. of Oncology, at 12 weeks (end of run-in period before start of daratumumab intervention) and at 20 weeks (after the fourth daratumumab injection), 32 weeks and at end-of-study at 52 weeks.

At these visits (12, 20, 32, and 52 weeks) a clinical assessment with laboratory test will be performed, in addition to collection of self-report questionnaires and blood samples for biobank.

Patients will also be assessed by clinical examination and laboratory tests before each daratumumab injection at 14, 16 and 18 weeks. An investigator or study nurse will contact the patient by telephone 2 days before daratumumab injections number 2, 3 and 4, and the physician will assess the patient upon arrival at the outpatient clinic for planned daratumumab injections 2, 3 and 4.

The study nurse will record any complaints or side effects from intervention, and the investigators will assess the CTCAE grading.

To make participation in the pilot study less demanding for patients, further monthly assessments at 24, 28, 36, 40 and 44 weeks can be performed by telephone provided that the

patients experience no significant side effects. However, if the patient experiences significant side effects – i.e. side effects of CTCAE grade > 1, which require clinical examination and/or extra laboratory work-up, these visits should also be performed in the outpatient clinic.

The patients should use effective contraception measures from 4 weeks before start of intervention and until 24 weeks after last intervention (i.e. week 44).

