In the intervention period (weeks 12-18) and for the following 14 weeks (i.e. until week 32) female patients of child-bearing potential must use highly effective contraceptive measures, and in this time interval the patients must perform a monthly serum pregnancy test (weeks 12, 16 and 20). Thereafter, in the time interval 24-32 weeks, pregnancy tests can be taken according to clinical indication.

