**In addition:**

At the **20-week visit**, plasma samples for determination of anti-daratumumab antibodies will be collected.

At the visits at **12, 16 and 20 weeks, and if given maintenance at weeks 26, 34 and 42:** s-HCG.

At the visits at **weeks 14, 16, 20, 32 and 52, and if given maintenance at weeks 26, 34 and 42:** serum immunoglobulins (IgG, IgA, IgM) and lymphocyte subtypes in peripheral blood (CD19, CD3, CD4, CD8, CD56/16, ratio CD8/CD4).

Also at the **52 week visit:** IgG subclasses (IgG1, 2, 3 and 4), and vaccination status with titers of antibodies to tetanus, diphtheria, pertussis and Covid-19.

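### The printed end of contraception, week 44, is 22 weeks too early for patients who complete maintenance, and the stricter contraception period ends before two of their injections

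*Protocol*

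**What the plan says.** **The 24-week rule.** The Protocol section Women of childbearing potential requires effective contraception for "at least 24 weeks following the administration of the last daratumumab injection" and gives no week number. It sets a matching 24 weeks after intervention for men. Assessment during follow-up repeats the 24 weeks for the patients in general and turns it into a week: "and until 24 weeks after last intervention (i.e. week 44").

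**The stricter period.** Later in the same section, women of childbearing potential must use highly effective measures over this span: "In the intervention period (weeks 12-18) and for the following 14 weeks (i.e. until week 32"). No maintenance equivalent is given.

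**The dosing.** The standard course ends at week 18. Under Design, if the four additional patients improve by week 24, "they will receive three additional maintenance daratumumab injections at weeks 26, 34 and 42". End of study gives the same three weeks. For the first two patients, Daratumumab intervention places two injections two weeks apart, "followed by an observation period of four to six weeks", and then two more injections two weeks apart.

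**What was updated for maintenance.** Fitbit recording continues "for the remaining 24 weeks (or 44 weeks if given maintenance) of the study", which is a duration (28 + 44 = week 72). Serum pregnancy tests are listed at "12, 16 and 20 weeks, and if given maintenance at weeks 26, 34 and 42". The laboratory tests before injections also name weeks 26, 34 and 42.

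**The concern.** Week 44 is offered as the calendar equivalent of 24 weeks after the last injection, but a patient who completes maintenance receives that injection at week 42. The instruction therefore contradicts itself for this group, and it also contradicts Women of childbearing potential. The sentence is addressed to the patients without restriction, in a section that itself describes the three extra injections and follow-up to week 72. It cannot easily be read as applying only to the original six.

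The stricter requirement has a related gap. It defines the intervention period as weeks 12-18 and ends at week 32, although two maintenance injections come later.

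The stake is participant safety. Someone who acts on the printed week would let contraception stop 2 weeks after an injection. Week 44 is also a scheduled telephone consultation in the maintenance schedule, which is a natural moment to apply it.

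**Working it through.** **Inputs, all from the Protocol**

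- Effective contraception: last injection + 24 weeks (Women of childbearing potential; Assessment during follow-up). Printed as week 44.
- Highly effective contraception: end of dosing + 14 weeks (Assessment during follow-up). Printed as week 32.
- Last injection, standard course: week 18.
- Last injection, first two patients: 12 + 2 + (4 to 6) + 2 = week 20 to 22 (Daratumumab intervention).
- Maintenance injections: weeks 26, 34 and 42 (Design; End of study).

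**Reproducing the printed weeks**

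- Week 32 reproduces for the standard course: 18 + 14 = 32.
- Week 44 does not: 18 + 24 = 42. It fits only a last injection at week 20 (20 + 24 = 44), one end of the range for the first two patients.

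**Each dosing pattern against the printed weeks**

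Weeks short = rule minus printed week; a negative value is on the safe side.

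| Pattern | Last injection | +24 weeks | Short of 44 by | +14 weeks | Short of 32 by |
|---|---|---|---|---|---|
| Standard course | 18 | 42 | -2 | 32 | 0 |
| First two patients, 4-week gap | 20 | 44 | 0 | 34 | 2 |
| First two patients, 6-week gap | 22 | 46 | 2 | 36 | 4 |
| Maintenance stopped after week 26 | 26 | 50 | 6 | 40 | 8 |
| Maintenance stopped after week 34 | 34 | 58 | 14 | 48 | 16 |
| Full maintenance | 42 | 66 | 22 | 56 | 24 |

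**Distance from the maintenance injections**

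- Week 44 is 44 - 42 = 2 weeks after the last maintenance injection.
- Week 32 is 34 - 32 = 2 weeks before the second maintenance injection and 42 - 32 = 10 weeks before the third.

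**Illustration of exposure.** Daratumumab dosing and administration gives a half-life of 20.4 days for subcutaneous monotherapy. Assume single-exponential decay of one dose from the day of injection, ignoring absorption and earlier doses. The fraction of the week-42 dose left at week 44 (14 days) is then 2^(-14/20.4), about 62%. After the full 24 weeks (168 days) it is 2^(-168/20.4), about 0.3%. This only shows the order of difference between the two stopping points.

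**The case against.** The strongest reply is that the governing rule is right. Women of childbearing potential is the dedicated section, it uses mandatory wording, and it counts from the last injection with no week number. Week 44 is a parenthesis added to a correct rule. This stands: read properly, the rule already takes maintenance patients to week 66, so the 22 weeks describe the printed figure and not the requirement. It does not excuse a wrong number in an operative instruction.

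A second reply is that the stricter period should be read in the same generous way, with maintenance counted as intervention and the 14 weeks running from it. That reading is strained, because the text defines the intervention period as weeks 12-18 and then deals with weeks 24-32 separately. A related point is that the only list of methods, in Women of childbearing potential, is of highly effective ones, so effective and highly effective may not have been meant as two tiers. Assessment during follow-up does give them different end points, but the drafting is unclear, and that is itself a reason to clarify it.

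Third, a serum pregnancy test accompanies each maintenance injection, and tests on clinical indication are scheduled at weeks 48 and 52. This lowers the risk of dosing during pregnancy. It does not replace contraception and leaves weeks 53 to 66 without a scheduled test.

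Fourth, patients work from the information sheet, which was reissued with version 1.4 and is not shown. Whether patients would see week 44 is therefore unknown; study staff would.

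Finally, Safety board/safety review puts completion of the first two patients' four injections at weeks 18-20, which conflicts with the four-to-six-week gap. At week 18 the printed week 44 would be 2 weeks safe, and at week 20 exact. The figures for those two patients are therefore uncertain; the maintenance result does not depend on them.

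**Conclusion.** The point holds: both contraception weeks are wrong or incomplete as written for maintenance patients. With all three maintenance injections given, week 44 is 22 weeks short of the 24-week rule, and week 32 is 24 weeks short of the stricter rule's own 14 weeks. If maintenance stops early, the shortfall against the 24-week rule is 6 weeks (last injection at week 26) or 14 weeks (week 34). The result for the stricter period rests on taking the stated weeks 12-18 at face value.

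The reach is narrow. At most four patients can receive maintenance, only if they improve by week 24, and only those to whom contraception applies are affected. For the standard course neither week falls short. No endpoint, sample-size figure or analysis changes. It should still be corrected, because it is a safety instruction that contradicts itself and the correction is simple.

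**What to change.** 1. In Assessment during follow-up, delete the parenthesis giving week 44 and state that the 24 weeks run from each patient's own last injection. This covers every pattern, including maintenance stopped early. If week numbers are wanted, give week 42 for the standard course, weeks 44-46 for the first two patients (after confirming their actual dosing weeks) and week 66 for full maintenance.
2. In the sentence on highly effective measures, extend the period through maintenance dosing plus the same 14 weeks, that is, to week 56 when the last injection is at week 42. Say at the same time whether effective and highly effective are meant as different requirements.
3. Check that the patient information carries the same dates.

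The cost is two sentences in the next protocol version and one document check. There is no cost to data or analysis.

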**At 12, 20, 32 and 52 weeks:**

Laboratory tests: Hemoglobin, leucocytes with differential count, thrombocytes, CRP, Na, K, Ca, Mg, phosphate, glucose, creatinine, eGFR, ALAT, ALP, GT, bilirubin, albumin.

At these visits, blood samples for biobank will be collected.

**At 14, 16 and 18 weeks (before daratumumab injections), and at weeks 26, 34 and 42 if given daratumumab maintenance:**

Laboratory tests: Hemoglobin, leucocytes with differential count, thrombocytes, CRP, Na, K, Ca, Mg, phosphate, glucose, creatinine, eGFR, ALAT, ALP, GT, bilirubin, albumin.

**In addition:**

At the **20-week visit**, plasma samples for determination of anti-daratumumab antibodies will be collected.

At the visits at **12, 16 and 20 weeks, and if given maintenance at weeks 26, 34 and 42:** s-HCG.

At the visits at **weeks 14, 16, 20, 32 and 52, and if given maintenance at weeks 26, 34 and 42:** serum immunoglobulins (IgG, IgA, IgM) and lymphocyte subtypes in peripheral blood (CD19, CD3, CD4, CD8, CD56/16, ratio CD8/CD4).

Also at the **52 week visit:** IgG subclasses (IgG1, 2, 3 and 4), and vaccination status with titers of antibodies to tetanus, diphtheria, pertussis and Covid-19.

**Data registration and management**

The recorded questionnaires (SF36, DSQ-SF, Function level), the weekly downloaded Fitbit data (steps per 24 hours, resting heart rate, heart rate variability) and any adverse events of CTCAE grade 2 or higher, will be registered in the CRF.

### Fitbit charge 4 data

Patients will receive a Fitbit Charge 4 armband at study start, with detailed instructions. The patients will be instructed to use Fitbit continuously except when recharging once weekly. Fitbit activity data from each participant will be downloaded at the study centre weekly, using the Fitbit web API (<https://dev.fitbit.com/build/reference/web-api/developer-guide/application-design/>)

After our randomized, placebo-controlled and double-blind trial with rituximab proved negative (11), we have worked to improve the design of future intervention trials in ME/CFS. We recently performed an observational study of 27 ME/CFS patients over 6 months, without intervention, using QoL and disease-specific questionnaires as well as continuous monitoring of steps and resting heart rate.

We will use the set-up from the Fitbit activity study (as yet unpublished). The study was approved by the Regional Committees for Medical and Health Research Ethics in Norway (REK No. 28780). A Data Protection Impact Assessment was performed in consultation with the IT Security Manager and Data Protection Officer for the Bergen Hospital Trust and user representatives.

Fitbit's terms of use comply with the General Data Protection Regulation (GDPR) directive. In order to protect the participants' privacy, we will use pseudonymisation toward third parties. Each participant Fitbit account will be set up using a study-specific e-mail address, initials instead of name and a fictitious date of birth.

### Near-Infrared Spectroscopy (NIRS) at baseline and during follow-up

We are currently in the process of testing a method for non-invasive measurements of tissue oxygenation using Near-Infrared Spectroscopy (NIRS) technology. NIRS measurements may be performed at baseline and repeated in the intervals 12-14 weeks, 20-24 weeks and 48-52 weeks. NIRS measures in real time the relative oxyhemoglobin and deoxyhemoglobin concentrations in the tissue at a distance approximately 1,5 cm below the probe, and provides an estimate of tissue oxygenation. We will measure tissue oxygenation at rest, continuously through a standardized repeated exercise, and during recovery. The exercise lasts for one minute followed by two minutes rest and is repeated twice. Volunteers who have tested the method have tolerated this limited exercise well.

### Monitoring

The pilot study will be monitored by the Section for research and innovation at Haukeland University Hospital

### Biobank samples during follow-up

**At 12, 20, 32 weeks:**

**If receiving additional maintenance injections: at weeks 12, 20, 34, 42:**

1 x 6 ml EDTA-Plasma

2 x 10 ml Serum

**At 52 weeks**

1 x 6 ml EDTA-Plasma  
1 x 6 ml EDTA-Blood  
3 x 10 ml Serum  
2 x 9 ml Tempus Blood RNA

### Blood sample collection for the biobank

The biobank form is marked with personal ID and patient study ID. Corresponding vacutainers are marked with patient study ID only.

Sample collection are performed in the following order:

Serum, BD Vacutainer Clot Activator Tube, red top

Plasma, Vacuette K2EDTA, purple top

Blood, Vacuette K2EDTA, purple top

Blood, RNA, Applied Biosystems TEMPUS Blood RNA Tube, blue top

Serum and EDTA-tubes are turned upside down 10 times after blood collection. Tempus tubes must be shaken vigorously for at least 20 seconds after blood collection, until a black color appears.

### Baseline 0 weeks, and 52 weeks

**3x10 ml serum**, BD Vacutainer Clot Activator Tube, red top

- Let coagulate for minimum 30 minutes, to avoid hemolysis during spinning.
- Spin at 1500xg, 10 minutes at room temperature.
- aliquot serum, 0,5 mL, on ice

**1x6 ml Plasma**, Vacuette K2EDTA, purple top

- Leave for maximum 1 hour at room temperature.
- Spin at 1500xg, 10 minutes, at room temperature.
- aliquot plasma, 0,5 mL, on ice.

**1x6 ml Blood**, Vacuette K2EDTA, purple top

**2x9 ml Blood, RNA**, Applied Biosystems TEMPUS Blood RNA Tube, blue top

All Serum-aliquots, plasma-aliquots, EDTA-blood (6 mL) and TEMPUS Blood RNA-tubes are stored at -80°C.

### At 12, 20, 32 weeks (or at 12, 20, 34, 42 weeks if given maintenance)

**2x10 ml serum**, BD Vacutainer Clot Activator Tube, red top

- Let coagulate for minimum 30 minutes, to avoid hemolysis during spinning.
- Spin at 1500xg, 10 minutes at room temperature.
- Aliquot serum, 0,5 mL, on ice

**1x6 ml Plasma**, Vacuette K2EDTA, purple top

- Leave for maximum 1 hour at room temperature.
- Spin at 1500xg, 10 minutes at room temperature.
- aliquot plasma, 0,5 mL, on ice.

Serum-aliquots and plasma-aliquots are stored at -80°C.

## Adverse events and Safety board

### Adverse events

Investigators will assess and classify adverse events (AE), serious adverse events (SAE), and SUSAR (suspected unexpected serious adverse reactions) according to the Common terminology criteria for adverse events (CTCAE), version 5.0 and the study drug SmPC.

For the purpose of safety and toxicity assessment, adverse events from grade 2 (moderate) and upwards, with possible, probable or certain causal relationship with the study drug will be reported. All SAE will be reported, regardless of causality.

Elective or pre-planned hospital admissions arranged prior to the start of study, or planned hospital admissions for trial specific procedures or treatment are not considered SAE.

Definitions and procedures for assessments and reporting of adverse events are described in appendix 1.

